## Abstract

**Background:**

The incidence of strokes in industrialized nations is on the rise, particularly in the older population. In Canada, a minority of individuals who have had a stroke actually receive intensive rehabilitation because most stroke patients do not have access to services or because their motor recovery was judged adequate to return home. Thus, there is a considerable need to organize home-based rehabilitation services for everyone who has had a stroke. To meet this demand, telerehabilitation, particularly from a service center to the patient’s home, is a promising alternative approach that can help improve access to rehabilitation services once patients are discharged home.

**Methods/Design:**

This non-inferiority study will include patients who have returned home post-stroke without requiring intensive rehabilitation. To be included in the study, participants will: 1) not be referred to an Intensive Functional Rehabilitation Unit, 2) have a Rankin score of 2 or 3, and 3) have a balance problem (Berg Balance Scale score between 46 and 54). Participants will be randomly assigned to either the teletreatment group or the home visits group. Except for the delivery mode, the intervention will be the same for both groups, that is, a personalized Tai Chi-based exercise program conducted by a trained physiotherapist (45-minute session twice a week for eight consecutive weeks). The main objective of this research is to test the non-inferiority of a Tai Chi-based exercise program provided via telerehabilitation compared to the same program provided in person at home in terms of effectiveness for retraining balance in individuals who have had a stroke but do not require intensive functional rehabilitation. The main outcome of this study is balance and mobility measured with the Community Balance and Mobility Scale. Secondary outcomes include physical and psychological capacities related to balance and mobility, participants’ quality of life, satisfaction with services received, and cost-effectiveness associated with the provision of both types of services.

**Study/trial registration:**

ClinicalTrials.gov: NCT01848080

## Background

The incidence of strokes in industrialized nations is on the rise, particularly in the older population. The risk of stroke doubles every ten years after age 55 [1]. The prognosis of functional recovery following a stroke depends on several factors, including initial severity of the injury, spontaneous recovery capacities and the impact of rehabilitation [2]. In older individuals, stroke sequelae can include sensorimotor, cognitive and perceptual impairments, which directly affect mobility and balance and thus drastically increase the risk of falls [3,4]. In fact, balance and ambulation problems are the most important fall risk factors following a stroke [5-7]. It has been shown that 75% of individuals who have had a stroke fall within the first six months following their discharge from hospital [3]. Consequently, balance is considered to be one of the most promising reversible risk factors to reduce falls [8,9].

In Canada, only 10 to 15% of people who have had a stroke actually receive rehabilitation services [10]. Typically, rehabilitation is based on a multidisciplinary approach that begins during acute care and continues in an intensive functional rehabilitation unit (IFRU) and after discharge. However, 37% of moderate-to-severe cases are transferred to a rehabilitation unit post-stroke [11]; the others return home with or without rehabilitation services [12,13], either because they live too far from a rehabilitation center or because their motor recovery was judged adequate for a safe return home [14,15]. Thus, there is a large number of individuals at home who need rehabilitation following their stroke but who do not have access to services [16]. Consequently, their mobility and balance decline, creating a significant risk for falls in this population.

The literature supports the need for outpatient rehabilitation services, at home or elsewhere for those who return home, regardless of the severity of their sequelae [17]. Unfortunately, the precarious nature of services has been well-documented in the Canadian Best Practice Recommendations for Stroke Care (updated 2013); it appears that the primary obstacle hindering best practice application in stroke care is the lack of human resources. With this in mind, the Best Practices Expert Consensus Panel prioritized certain recommendations, including facilitating outpatient and home-based rehabilitation services because of the inability of the healthcare system to meet current demands [18]. Therefore, it is essential to improve accessibility to rehabilitation services, as clearly indicated in the Quebec Homecare Support Policy [18,19].

In this context, new alternative approaches need to be considered to deliver services at home. Telerehabilitation, defined as a telehealth application that uses telecommunication technologies to provide rehabilitation services, is a new approach in the rehabilitation field. It has been identified as a very promising alternative tool that could help improve access to healthcare services in general [20-25]. Furthermore, telerehabilitation has been identified as one of the three telehealth application areas prioritized by the Quebec Ministry of Health and Social Services [11]. A main advantage of this intervention method is that it allows patients to receive rehabilitation in their homes without having to travel to get healthcare services. This way of delivering services also addresses the shortage of professionals; with less time spent traveling, professionals can spend more time treating, which in turn improves access to services. It is therefore crucial to provide decision-makers with evidence concerning the effectiveness of telerehabilitation applications.

Regardless of the rehabilitation delivery mode, the choice and type of exercise program varies from one study to the next. Recent studies have shown that a balance retraining program based on Tai Chi movements improved balance in individuals at risk of falls [26,27]. A Tai Chi-based exercise program, supervised by a physiotherapist, which uses movement repetition favoring directional adjustments in space has been shown to be effective in improving balance in individuals with physical impairments, including those presenting sequelae following a stroke. Two studies conducted by our research group demonstrated similar results in frail, older individuals [28,29]. A study conducted with older individuals with diabetes found that a simple sequence of Tai Chi movements improved their balance and attention capacity [29]. Another study conducted with frail, older individuals with balance problems showed that a Tai Chi intervention had a protective effect on the incidence of falls: for every person who had falls in the Tai Chi group, the conventional physiotherapy group had 1.3 people who had falls [29]. Furthermore, the Tai Chi intervention appeared to delay the onset of the first fall in older individuals, with 50% of participants in the physiotherapy group falling once after five months of follow-up, compared to after ten months of follow-up for 50% of participants in the Tai Chi group [30]. Even more interesting is the fact that these balance retraining programs based on Tai Chi movements are equally effective in older individuals following a stroke [31,32]. In fact, the first large-scale study [31] (Tai Chi group: n = 74; comparison group: n = 62) demonstrated the effectiveness of Tai Chi in improving balance compared to a conventional exercise program in individuals with chronic stroke. A second study [32] achieved the same results with 18 patients. Moreover, in a pre-/post- intervention study with no control group, 17 balance impaired elders have undergone a structured, interactive, and supervised Tai Chi class from their own homes through a videoconferencing system to improve balance and reduce fear of falling. The results demonstrated the intervention was effective for improving balance and reducing fear of falling [33]. Finally, our pilot study demonstrated that Tai Chi practiced via supervised telerehabilitation was effective in improving balance and motor skills in six patients post-stroke.

The principal aim of this clinical trial is to test the non-inferiority of a Tai Chi-based exercise program, provided via telerehabilitation compared to the same program provided in person at home, in terms of effectiveness for retraining balance in individuals who have had a stroke but do not require intensive functional rehabilitation. More specifically, the objectives are to:

1) Verify whether the gains in both physical and psychological capacities related to balance and mobility of patients treated by Tai Chi via telerehabilitation are not inferior to those receiving the same treatment in person at home;

2) Verify if the gain in quality of life of patients treated by Tai Chi via telerehabilitation is not inferior to the gain of those receiving the same treatment in person at home;

3) Verify if satisfaction with services received by patients treated by Tai Chi via telerehabilitation group is not inferior to satisfaction of those receiving the same treatment in person at home;

4) Compare the costs associated with the provision of the two types of services delivery, that is, via telerehabilitation and in person at home.

## Methods/Design

### Study design

The design of choice to determine the effectiveness of an experimental intervention compared to a standard intervention is the randomized controlled trial (RCT). Two groups will be formed: 1) telerehabilitation group, and 2) home visits group. We will use this design while considering that the prerequisites for undertaking a non-inferiority RCT are met:

1) The plausibility that a balance retraining program based on Tai Chi movements has been shown to improve balance [34], and specifically in clients with stroke [32,35].

2) The research procedures in telerehabilitation are well established in real-life situations, from both clinical and technological perspectives. Our team is at the forefront of conducting studies in home-based teletreatment following knee arthroplasty [30,36], in speech therapy [37], and in individuals with chronic obstructive pulmonary disease [38].

3) We conducted a pilot study in six patients post-stroke.

Figure 1 illustrates the research design and timeline.

**Figure 1 F1:**
[figure not shown]
Research design and timeline.

### Participants

The study population of interest will be individuals who have had a stroke and stayed in a hospital linked to one of the following sites: 1) Sherbrooke site (Centre Hospitalier Universitaire de Sherbrooke), 2) Montreal sites (Jewish Rehabilitation Hospital, Institut de Réadaptation Gingras-Lindsay-de-Montreal and Centre de Santé et de Services Sociaux Champlain-Charles-Le Moyne), and 3) Toronto site (Sunnybrook Health Sciences Center). Special care will be taken to ensure that participant eligibility will target individuals who have had a stroke and returned home without requiring intensive rehabilitation. We will base our selection on the Rankin classification [39] established by the treating neurologist or trained therapist during the hospitalization period. This classification system allows us to assign individuals who have had a stroke to one of four groups according to their level of functional impairment. Patients with a Rankin score of 2 generally present with mild impairments, maintain their autonomy and can perform all previous activities. Patients with a Rankin score of 3 present with moderate impairments and generally require moderate assistance with their activities of daily living. These patients are usually sent home with or without referral for physiotherapy services at home.

Therefore, a sample of participants aged 45 years and older will be recruited based on the following inclusion criteria: 1) have had a stroke with a Rankin score of 2 or 3; 2) not be referred to an IFRU and return home following discharge from hospital; 3) understand instructions to allow participation in evaluations and interventions; 4) have a balance problem as evidenced by a score between 46 and 54 on the Berg Balance Scale [40]; 5) have a caregiver who would be available during the telerehabilitation sessions to ensure safety during exercises; and 6) live in an area served by high speed Internet. Excluded will be individuals who present with: 1) a previous stroke episode in the last 12 months (other than the present one); 2) severe body hemineglect; 3) significant hemianopsia visual problems accompanied by hemineglect; 4) uncontrolled medical problems; and 5) moderate to severe aphasia.

Participants will be recruited during the hospitalization period by the team of treating nurses, physiotherapists and neurologists at each of the three sites (Sherbrooke, Montreal and Toronto). When the team decides that a patient will not require a referral to an IFRU and will return home (inclusion criteria 1 and 2), they will verify inclusion criteria 3 and 4 and exclusion criteria 1 to 5 from the medical chart. If patients are eligible based on these criteria, the hospital team will ask if they agree to be contacted by a research associate. If they agree, a research associate will visit them in hospital to inform them of the project and ask them to participate. The research associate will verify inclusion criteria 5 and 6. If a patient meets all the criteria and is interested in participating in the study, they will be asked to sign the consent form previously approved by the ethics committee at each recruitment site.

Once included, participants will be randomly assigned to either the telerehabilitation group or the home visits group by the coordinator of each recruitment site. This randomization will be performed using block randomization of sizes 2 and 4 done by a computer. Block size will not be known by the evaluators. This randomization will be performed following stratification based on the Rankin score (2 or 3), a variable that is likely to influence recovery prognosis. A system of numbered, sealed envelopes will be put in place.

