### Outcomes

All evaluations will be completed in the research centers/hospitals of the three sites and will last approximately three hours. The first evaluation will be conducted at baseline, prior to starting intervention (T_1_) to collect base measures on the participants’ condition. A second evaluation will be conducted just after the two-month intervention (T_2_) and the third evaluation will be four months (T_3_) following discharge from the hospital. All evaluations will be carried out by evaluators trained in the standard procedures for all measures, who are independent and blinded to the intervention. Specific directions will be provided to the evaluators and the participants to ensure that intervention allocation remains anonymous.

To measure balance and functional mobility, the Community Balance and Mobility Scale (CB&M) [43-45] will be used. This tool was developed for ambulatory individuals following a traumatic brain injury [43]. It has been validated in individuals following a stroke [44,46]. It assesses 19 tasks. The items are rated on a six-point scale (from 0 = unable to perform, to 5 = able to perform independently), for a maximum total score of 95 points. The CB&M has demonstrated good intra-rater, inter-rater and test-retest reliability (ICC = 0.98 for all three cases) and high internal consistency (Cronbach’s alpha = 0.96) [43]. It has good convergent validity with the Chedoke-McMaster Stroke Assessment [47] for leg and foot (r = 0.61 and 0.63, respectively) and for lower extremity strength (r = 0.67) [44]. Furthermore, the CB&M has been shown to be sensitive to change from baseline at follow-up in community-dwelling, ambulatory individuals post-stroke (SRM (standardized response mean) = 0.83) [44]. In addition, the Berg Balance Scale [42,48] will be used to evaluate balance in patients. The Four-Squares Test will also be used. This test consists of moving in different preset directions: forward, backward and to the sides. The time required to complete the sequence is recorded. An execution time greater than 15 seconds is predictive of falling. This test has high inter-rater (ICC = 0.99), intra-rater (ICC = 0.98) and test-retest (ICC = 0.98) reliability in community-dwelling older individuals aged 65 years and over [49]. Also, for predicting falls, this test has good specificity ranging from 88% to 100% and a positive predictive value of 86% [49].

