### Statistical methods

We expect to recruit 240 participants, that is, 120 per group. Allowing for a drop-out rate of 10%, this sample size will provide a power of 80% to demonstrate the non-inferiority of Tai Chi provided by telerehabilitation compared to Tai Chi provided in person at home, with a two-group one-sided test at the 2.5% level (nQuery Advisor 7.0; Statistical Solutions, Boston, MA). For this calculation, the non-inferiority limit was set at four points on the CB&M scale and the standard deviation of the gain was estimated to be 10.4, based on findings from Knorr [44], since SRM = Mean_GAIN_/s_GAIN_ implies that:

$$S_{\mathrm{GAIN}}={\mathrm{Mean}}_{\mathrm{GAIN}}/\mathrm{SRM}=\left(51.3-42.7\right)/0.83$$

First, we will describe the characteristics of each group pre-intervention using averages and standard deviations (continuous variables) or percentages (categorical variables). The groups will then be compared using a *t*-test or chi-squared test. If the groups differ on certain characteristics pre-intervention despite randomization, subsequent analyses will account for these differences.

Primary analysis will aim to test the non-inferiority of Tai Chi provided via telerehabilitation compared to Tai Chi provided in person at home as evaluated by score gains on the CB&M questionnaire from T1 to T2. Delivery by telerehabilitation will be regarded as non-inferior to in person home delivery if the upper limit of the unilateral confidence interval around the difference in gains between the two groups is less than 4. This non-inferiority limit was set below the CB&M’s minimal clinically significant difference of five points. It is recommended to choose a non-inferiority limit less than the difference judged to be clinically significant [74,75].

The same analytical strategy will be used to evaluate and compare the effectiveness of the interventions on secondary variables and to compare maintenance over time (that is, the confidence interval around the difference between the two groups from T1 to T3) across all variables. A more conservative level of significance will be used to account for the numerous tests.

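### Site coordinators allocate locally, but Rankin is the only stratification factor named and the primary comparison has no site term: a small, cheaply recovered loss of precision

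*Protocol article*

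**What the plan says.** In the Participants section, recruitment takes place "at each of the three sites (Sherbrooke, Montreal and Toronto"), and the same section names five hospitals within those three sites. It then says that "participants will be randomly assigned to either the telerehabilitation group or the home visits group by the coordinator of each recruitment site". On the method: "This randomization will be performed using block randomization of sizes 2 and 4 done by a computer". On stratification: "This randomization will be performed following stratification based on the Rankin score (2 or 3"), with the reason that Rankin probably affects prognosis. No other factor is named. On concealment: "A system of numbered, sealed envelopes will be put in place". Whether there is one envelope series or one per site is not said. Block size is to be kept from the evaluators; the coordinators are not mentioned.

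Under Outcomes: "All evaluations will be completed in the research centers/hospitals of the three sites".

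Under Statistical methods, the primary analysis is a one-sided confidence limit for the difference between two groups "as evaluated by score gains on the CB&M questionnaire from T1 to T2", compared with a limit of 4 points. Neither site nor Rankin is a term in it. The only adjustment foreseen there, repeated in the Discussion, applies if the groups turn out to differ at baseline. Site is not named.

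**The concern.** Site is built into how this trial allocates and measures, but appears neither in the stated stratification nor in the stated comparison. What follows depends on how the envelopes are organised:

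- **One Rankin list shared between sites.** Nothing balances the arms within a site, and the blocks of 2 and 4 are split across sites.
- **A separate series at each site.** The trial is then in effect stratified by site, but the planned interval still counts between-site variation as error.

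There is some reason to expect sites to differ. The Discussion gives the numbers of stroke admissions that returned home: 59/269 (22%) at Sherbrooke, 60/106 (57%) at Champlain-Charles-Le Moyne and 49/189 (26%) at Toronto. Returning home is an inclusion criterion, so the case mix of eligible patients may differ. These figures do not show that CB&M gain differs by site.

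At stake is a modest amount of precision in a non-inferiority trial planned at 80% power.

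**Working it through.** **Inputs from Statistical methods.** Limit 4 points; SD of gain 10.4 (from 8.6/0.83 = 10.36); one-sided 2.5%; power 80%; drop-out 10%; 120 per arm, so 120 × 0.9 = 108 evaluable per arm.

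**The plan's own figure.** n per arm = 2 × (1.960 + 0.842)² × 10.4² / 4² = 106.1, so 107; 107/0.9 = 118.9, so 119. With the noncentral t distribution n is 108, and 108/0.9 = 120. The stated 240 reproduces.

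**Assumption.** R², the share of the variance of gain explained by site, is not in the documents. The range 0 to 0.10 is used, with 10.4 taken as the total SD.

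**Precision with balanced arms and site in the model** (normal approximation). Without site, SE = 10.4 × √(2/108) = 1.415 and the half-width is 1.96 × 1.415 = 2.77. With site, SE is multiplied by √(1 − R²), and power = Φ(4/SE − 1.96).

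| R² | SE | Half-width | Power | n per arm for 80% |
|---|---|---|---|---|
| 0 | 1.415 | 2.77 | 80.7% | 107 |
| 0.02 | 1.401 | 2.75 | 81.5% | 104 |
| 0.05 | 1.379 | 2.70 | 82.6% | 101 |
| 0.10 | 1.343 | 2.63 | 84.6% | 96 |

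The gain over 80.7% is 0.8, 1.9 and 3.9 points for R² of 0.02, 0.05 and 0.10.

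**Site-specific lists, site left out of the analysis.** The estimate varies with the smaller SE, but the interval uses 1.415. The true one-sided error is then 1 − Φ(1.96/√(1 − R²)): 2.4%, 2.2% and 1.9% for R² of 0.02, 0.05 and 0.10. The test is conservative. At R² = 0.10, power is Φ((4 − 2.774)/1.343) = 81.9%, against 84.6% with site in the model.

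**Simulation** (3,000 trials per setting; 216 patients; blocks of 2 and 4; three or five equally likely sites; no effect of Rankin on gain). The simulation standard error is about 0.3 points for error rates and 0.7 points for power.

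- *Balance.* With one Rankin-only list, the largest gap between arms in any site's share averages 8 percentage points (95th percentile 14 to 15). With site-by-Rankin lists it averages 1 to 1.5 points (95th percentile about 2 to 2.5).
- *Error, Rankin-only list, unadjusted.* 2.2% to 3.0%, which is near 2.5% within simulation noise.
- *Error, site lists, unadjusted, R² = 0.10.* 1.9% to 2.0%, in line with the formula above.
- *Half-width, three sites, R² = 0.10.* Rankin-only list: 2.79 unadjusted, 2.66 with site. Site lists: 2.79 unadjusted, 2.64 with site. Nearly all of the gain comes from the model term.
- *Power gained by adjusting.* About 0 to 3.5 points for R² of 0.02 to 0.10. At R² = 0, between no change and a loss of about 1 point.

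**The case against.** The strongest reply is that the article is silent here, not wrong. How envelope series are organised and which covariates enter the model are details that a full protocol or analysis plan often holds, and neither is shown. Coordinators in three cities who hold physical envelopes suggest local series, in which case small blocks already balance each site and the unadjusted interval errs in the safe direction for a non-inferiority claim. The outcome is a within-person gain, so constant site or rater offsets largely cancel. Evaluators are trained and blinded, assessors are to be calibrated, and the article cites an inter-rater ICC of 0.98 for the CB&M. Finally, the conditional baseline adjustment could take in a marked imbalance by site.

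Much of this stands, and it keeps the point small. It does not remove it. The article does state a stratification scheme, with a reason for it, and it does state the primary comparison; site is in neither. The conditional adjustment depends on the data, does not name site, and would recover no precision when sites happen to be balanced.

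A reader might infer that imbalance by site could seriously move the estimate. Take five hospitals of 48 patients on one shared list. The SD of the arm difference in one hospital is √(48 × (1 − 48/240)) = 6.2, and 1.96 × 6.2 = 12.1 patients. If that hospital's mean gain differed from the rest by 5 points, the shift would be 12.1/120 × 5 = 0.5 point. But this combines a 95% extreme with a 5-point difference that has no source, and it applies only if the list is shared. A one-SD imbalance gives 6.2/120 × 5 = 0.26 point, against a standard error of about 1.4. Chance imbalance under randomisation is not bias, and the interval already allows for it.

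Nor do the documents establish that treatment is organised by site. The Interventions section says only that a physiotherapist trained in Tai Chi conducts the sessions.

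**Conclusion.** The point holds as a minor, optional improvement. Rankin is the only stratification factor named, although allocation is local, and the stated primary comparison leaves site out. Depending on how the lists are held, the consequence is either chance imbalance by site or an interval slightly wider than it need be.

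The size is about 0 to 4 points of power if site explains 2% to 10% of the variance of gain. That share is assumed, and the benefit disappears if it is zero. The documents do not support reading this as an inflated type I error, a biased estimate or too small a sample: simulated error stays near or below 2.5%, and 240 remains enough.

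The stratification statement is the firmer half, since the model term may be in an analysis plan that is not shown.

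**What to change.** In Participants, state how the lists are held, for example: *For participants still to be randomised, allocation is stratified by site (Sherbrooke, Montreal, Toronto) and Rankin score (2 or 3), with a separate computer-generated envelope series for each combination. Block sizes are concealed from the site coordinators as well as the evaluators.* Using the three sites instead of five hospitals avoids sparse strata.

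In Statistical methods, state: *The difference in CB&M gain from T1 to T2 is estimated with site and Rankin score as fixed terms, in both the ITT and the PP analysis.*

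Recruitment had begun when the article was written, so new lists can apply only to later participants. The model term can still be fixed before analysis, and it brings most of the benefit.

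Cost: six envelope series (3 sites × 2 Rankin levels) in place of two if a shared list is used now, and three model degrees of freedom (two for site, one for Rankin) out of 214. If site explains nothing, up to about 1 point of power is lost. Small blocks in local series are somewhat easier to predict, which is why the coordinators should not know the block sizes. No extra patients or visits are needed.
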